### **2.2.1 Secondary Objectives**

- To investigate the sustainability of the effect of a brain computer interface system for the treatment of inattentive symptoms of Attention Deficit Hyperactivity Disorder (ADHD).

- To investigate the effect of a brain computer interface on daily functioning.
- To investigate if there is any safety concern related to the use of BCI.

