### 2.3.1 Safety Endpoints

Adverse events and serious adverse events.

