## 4. Trial Schedule

During Pre-Screening, the parent/legal guardian will complete the structured interview, CDISC.

Once the diagnosis of ADHD (inattentive/combined subtype) has been made, the parent/legal guardian will complete the following questionnaires during the baseline stage (Week 1):

a. ADHD Rating Scale

b. Child Behavior Checklist

If the child has ever been placed in the school's Learning Support Program and/or is currently failing a subject, he/she will be screened using the Kaufman Brief Intelligence Test.

The assessment schedule is summarized in Table 1 section 6.6.

Once the diagnosis of ADHD has been made, the following assessments will be completed by different informants:

CLINICIAN:

1. ADHD Rating Scale (ADHD- RS)
2. Clinical Global Assessment Scale (CGAS)
3. Clinical Global Impression - Severity Scale (CGI-S)
4. Clinical Global Impression – Improvement Scale (CGI-I)
5. Pediatric Adverse Event Rating Scale (PAERS) from week 8 onwards as there will be nothing to report at the first session.

PARENT:

1. ADHD Rating Scale (ADHD-RS)
2. Child Behavior Checklist (CBCL)

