## **9. Safety Measurements**

### **9.1 Definitions**

#### **9.1.1 Adverse Events**

The Pediatric Adverse Event Rating Scale will be used to assess adverse events.

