#### **9.1.3 Serious Adverse Events**

A serious adverse event (experience) or reaction is any untoward medical occurrence that at any dose:

- results in death,
- is life-threatening,

- requires inpatient hospitalisation or prolongation of existing hospitalisation,
- results in persistent or significant disability/incapacity, or
- is a congenital anomaly/birth defect.

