## **9.2 Collection, Recording and Reporting**

### **9.2.1 AE**

AEs will be collected from the time the informed consent and assent forms have been signed until the end of the study. This will include AEs spontaneously reported by the subject and / or observed by the parents and clinicians.

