#### **11.2.3 Analysis of primary and secondary endpoints**

Change in the inattentive score on the ADHD Rating Scale as rated by clinicians at week 8 will be compared between the intervention group (post-BCI) and control groups (pre-BCI) using the two sample t test. Mean difference of the changes between the two groups and its associated 95% confidence interval will be reported. Comparison of change scores for the continuous secondary outcomes at week 8 between the two groups will also be conducted by using the two sample t test or Mann-Whitney U test, where appropriate. Chi squared test or Fisher's exact test, where appropriate, will be used for categorical secondary outcomes.

Booster effect will be analyzed by first pooling paired data before and after the boosters in the two groups. Change in efficacy endpoints as rated by clinicians and parents at week 20 from week 1 in the intervention arm and changes at week 28 from week 9 in the waitlist control group. These pooled changes before and after the boosters will be summarized; and comparisons of efficacy endpoints pre and post boosters will be made in the pooled data by using the paired t test or Wilcoxon signed rank test, where appropriate. The above will also be conducted at week 24 from week 1 in the intervention arm and week 32 from week 9 in the waitlist control to assess the effect the sustainability of the effect of the BCI system.

The longitudinal ADHD ratings, and other clinician's scales will be explored by the generalized estimating equations approach, both assessing the time trend and the difference in time trend between groups.

Frequency and percentage of the adverse events highlighted in the side effect checklist will be summarized for the pooled sample since the BCI program is administered to all subjects for all those that receive at least one BCI session.

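### The only safety summary stated in Section 11.2.3 draws on an undefined side effect checklist, a narrower source than the AE and SAE endpoint, so SAEs are not identified and events recorded only off the checklist are not summarised

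*Protocol*

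**What the plan says.** The protocol makes safety a secondary objective in Section 2.2.1: "To investigate if there is any safety concern related to the use of BCI". Section 2.3.1 gives the safety endpoint in full as "Adverse events and serious adverse events".

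On collection, Section 9.2.1 says "AEs will be collected from the time the informed consent and assent forms have been signed until the end of the study", and adds: "This will include AEs spontaneously reported by the subject and / or observed by the parents and clinicians". Section 9.1.1 names the instrument: "The Pediatric Adverse Event Rating Scale will be used to assess adverse events". Section 4 places it among the clinician assessments and sets its start: "Pediatric Adverse Event Rating Scale (PAERS) from week 8 onwards as there will be nothing to report at the first session". Table 1 in Section 6.6 schedules it at weeks 8, 20 and 24 for the intervention group and at weeks 16, 28 and 32 for the control group. SAEs have their own definition in Section 9.1.3, based on seriousness criteria and not tied to any scale: "A serious adverse event (experience) or reaction is any untoward medical occurrence that at any dose", followed by the criteria.

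On analysis, the last sentence of Section 11.2.3 is the only one that deals with safety: "Frequency and percentage of the adverse events highlighted in the side effect checklist will be summarized for the pooled sample". It pools the two arms and takes as its population the children who had one BCI session or more.

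**The concern.** The protocol does more than stay silent on safety analysis. It fixes the data source, the statistic, the pooling and the population, and the source it fixes is narrower than the endpoint. An SAP written to follow that sentence would carry the gap forward.

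At stake is the answer to the safety objective in children aged 6 to 12. Section 8.1 itself names seizure and destabilised mood as potential risks of BCI. Such an event can occur at any time. If it met a seriousness criterion, the stated summary would not show it as serious, and if it was recorded only outside the checklist, the summary would not show it at all.

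**Working it through.** The plan gives no figure to reproduce for this point, so the check sets the sections side by side.

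**1. What the checklist is.** The term side effect checklist occurs only in Section 11.2.3. The PAERS is the likely referent, because Section 9.1.1 names it for assessing AEs and no other safety instrument appears in Table 1. The steps below assume this.

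**2. What each section covers.**

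| Element | Endpoint or collection | Stated summary (11.2.3) |
|---|---|---|
| AE marked on the checklist | Yes (2.3.1, 9.1.1) | Counted |
| AE volunteered or observed, and also marked on the checklist | Yes (9.2.1) | Counted |
| AE volunteered or observed, never marked on the checklist | Yes (9.2.1) | Not counted |
| SAE marked on the checklist | Yes (2.3.1, 9.1.3) | Counted, but not identified as serious |
| SAE never marked on the checklist | Yes (2.3.1, 9.1.3) | Not counted |

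Sections 9.2.2 and 9.3 deal with reporting deadlines and with follow-up of individual children. Neither produces a trial-level result.

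**3. When the checklist is completed.** In Table 1 the first PAERS is at week 8 (intervention) or week 16 (control). Sections 5.1 and 5.2 spread the 24 sessions over 8 weeks, starting at week 9 in the control group. In both arms the first checklist therefore falls at about the end of the course. Section 3.3 continues assessments after a child stops training, unless the family leaves the study altogether. A child who attends some sessions and then leaves altogether before the first checklist still meets the condition of one BCI session, but has no form on which an event could be marked.

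**4. What such children could do to the percentage (illustration).** The documents do not say how many there will be. Let d be the share of the safety population with no checklist, and p the true share of children with an event, assumed equal in children with and without a checklist. The reported share is then p × (1 − d). Section 11.1 allows for up to 20% losses. That allowance covers losses of every kind, so d = 0.20 is an extreme case. With an assumed p of 10%:

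- d = 0: 10% × 1.00 = 10%
- d = 0.10: 10% × 0.90 = 9%
- d = 0.20: 10% × 0.80 = 8%

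The shortfall would be larger if children leave because of an event, a case that Section 9.3 foresees.

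**The case against.** The strongest reply has three parts.

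First, Section 11.2.3 does not say that nothing else will be summarised. SAE tables are commonly left to the SAP, which is not at hand and may contain one. This is right as far as it goes: the restriction follows from this being the sole safety analysis sentence, not from an express exclusion. But the sentence specifies its source, and an SAP that added SAE tables would be going beyond what the protocol states.

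Second, the PAERS is the protocol's chosen instrument for AEs, is completed by clinicians, and can pick up at the next visit an event volunteered earlier. This also stands, and it limits the point. A reader might infer that SAEs and spontaneously reported events reach no safety result at all. The documents do not support that, because any such event marked on the checklist would be counted. What remains is the loss of the seriousness label and of events never marked. That some events stay unmarked is plausible, though it is an inference: Section 6.5 blinds the assessing clinicians and tells families not to disclose the arm to them, so an event at a training session may reach unblinded staff and not the rater.

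Third, serious events are not lost, since they are reported and followed individually. That is true of case handling, but it gives no summary for the trial.

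It is also tempting to size the gap by comparing the number of training sessions with the number of checklists. That comparison sets reporting opportunities against forms. One form can cover the whole interval since the previous visit, so the ratio says nothing about the share of events captured.

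**Conclusion.** The point holds in limited form. The stated safety summary rests on a source narrower than the stated endpoint and the stated collection. Followed exactly, it does not identify SAEs, does not summarise AEs or SAEs recorded only outside the checklist, and can include children who had no opportunity to contribute an event.

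It does not show that serious or spontaneous events will be absent from the results: those marked on the checklist are counted, and an SAP could add more. Nor can the number of events missed be derived from the documents. The conclusion assumes that the checklist is the PAERS and that Section 11.2.3 is applied as written. If the checklist is some other form, the source of the summary is not specified at all. The primary efficacy comparison is unaffected. The text should be corrected before the safety data are analysed.

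**What to change.** In Section 11.2.3:

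- Say which form the side effect checklist is (the PAERS, if that is meant), and use one name throughout.
- State that all collected AEs, whether elicited by the checklist, spontaneously reported or observed, are summarised as the number and percentage of children with at least one event. This also gives children who leave before the first checklist a route into the numerator.
- State that SAEs are summarised separately and listed with arm and timing relative to the first BCI session. Timing is needed because collection starts at consent, while control children start BCI only at week 9.

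The cost is a short text change, one extra table and one listing. No new data are needed, because Section 9.2.1 already collects these events. The reported AE rate may come out slightly higher than under the present wording.

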## **12. Ethical Considerations**

The Principal Investigator has the sole responsibility in ensuring that this clinical trial will be conducted in accordance with the applicable laws and regulations and in accordance with the good clinical practices guidelines. Only the DSRB's approved version of the protocol, assent form and informed consent form will be used throughout the study. Any amendments or revisions to the study procedure and/or consent and assent forms will only be implemented after approval from the DSRB has been granted.

Participants will be paid \$40 for each interview done at baseline (week 1), and weeks 8, 20 and 24 for intervention group and weeks 1, 8, 16, 28 and 32 for control group . Participants will be paid \$10 per visit for all other scheduled trial visits.

### **12.1 Informed Consent by the Parent and Informed Assent by the Child**

A written informed consent by the parent/legal representative and a written informed assent form by the child will be obtained first before any subject is enrolled into this study. In obtaining and documenting informed consent and assent form, the Investigator or Co-investigator should adhere to the principles as stipulated in Singapore Guideline Good Clinical Practice (SGGCP).

Informed consent from parents and assent from children will be taken during the first clinic visit (pre-screening visit) at the clinic premises of the CGC. Only the Site Principal Investigator and those delegated by him to take informed consent and assent can conduct the consent process. The parents/legal guardians and subjects will be given time to consider their participation in the study. Verbal and written information given to the subject and parents/legal guardians shall be in simple terms and in a language understood by them. A copy of the signed and dated written informed consent and assent form will be provided to parent and subject/child.

To protect the privacy interests of the research participants, where “privacy interests” refer to interests of individuals to be left alone, free from intrusion and comfort with the proposed clinic settings, the child shall be accompanied by the parent/legal guardian during every visit to the clinic and all interventions will be performed in designated laboratory rooms within the clinic to ensure privacy.

## **12.2 Confidentiality of Data and Patient Records**

All electronic data will be password-protected and essential trial documents will be kept securely with locks.

Access to research study databases will be restricted. Only study staff and staff from Singapore Clinical Research Institute (SCRI) who are involved in conducting external monitoring visits will have access to study data files. Besides, NHG Domain Specific Review Board (DSRB) and the Ministry of Health will also have access to study database for audit purposes. All patient identifiers will be delinked, and the subjects will be assigned a number instead.

Atentiv Incorporated (USA), who holds the patent and license to the Brainpal™ technology, will have access to the data generated from the study. In addition, the study data may be provided to third parties, including commercial entities for commercial use. However, no personal information that could be used to identify you or your child will be disclosed to any of these parties and will remain confidential.

No part of the study procedures will be recorded on audiotape, film/video, or other electronic medium.

## **13. Publication Policy**

Publication of the results by the Investigator(s) is subject to mutual agreement between the Investigators and Institution. Manuscripts and abstracts must be sent to the institutional representative prior to submission.

## **14. Retention of Trial Documents**

After completion of the study SCRI will return all study documents to the Principal Investigator for archiving according to established Institutional policy and GCP guidelines.

## 15. Insurance

The study will be conducted at the Institute of Mental Health and as such will be covered by the NHG Clinical Trials Compensation Insurance. The intervention involved in this study is non-invasive and it is not expected to result in any form of injury.

## **17. Appendices**

### **17.1 List of Abbreviations**

|           |                                                                                            |
|-----------|--------------------------------------------------------------------------------------------|
| ADHD      | Attention Deficit Hyperactive Disorder                                                     |
| ADHD-RS   | Attention Deficit Hyperactive Disorder – Rating Scale                                      |
| AE        | Adverse Event                                                                              |
| BCI       | Brain-Computer Interface                                                                   |
| CBCL      | Child Behaviour Checklist                                                                  |
| C-DISC    | Computerized Diagnostic Interview Schedule for Children                                    |
| C-GAS     | Clinical Global Assessment Scale                                                           |
| CGC       | Child Guidance Clinic                                                                      |
| CGI-I     | Clinical Global Impression Improvement Scale                                               |
| CGI-S     | Clinical Global Impression Severity Scale                                                  |
| CONSORT   | Consolidated Standards of Reporting Trials                                                 |
| CPT       | Continuous Performance Test                                                                |
| CRA       | Clinical Research Associate                                                                |
| CRF       | Case Report Form                                                                           |
| DSM-IV TR | Diagnostic & Statistical Manual of Mental Disorders, 4 th Edition Text Revision |
| DSRB      | Domain Specific Review Board                                                               |
| EEG       | Electroencephalogram                                                                       |
| IQ        | Intelligence Quotient                                                                      |
| KBIT-2    | Kaufman Brief Intelligence Test, 2 nd Edition                                   |
| LSP       | Learning Support Program                                                                   |
| MCQ       | Multiple Choice Question                                                                   |

|         |                                                             |
|---------|-------------------------------------------------------------|
| NHG     | National Healthcare Group                                   |
| PAERS   | Pediatric Adverse Event Rating Scale                        |
| REACH   | Reaching Everyone for Active Citizenry at Home              |
| SCRI    | Singapore Clinical Research Institute                       |
| SGGCP   | Singapore Guideline for Good Clinical Practice              |
| TRF     | Teacher Report Form                                         |
| UPIRTSO | Unanticipated Problems Involving Risk To Subjects or Others |
